###### Effectiveness on Health Outcomes of Survivors of Burn Injuries – Secondary Outcome Measures

For the other outcome measures, we will perform similar multilevel analyses, testing the effects of baseline scores and intervention. In addition, we will calculate correlation coefficients to explore the association between the PiH and the SeRa. Correlation coefficients will be interpreted as negligible correlation (0‐0.3), low correlation (0.3‐0.5), moderate correlation (0.5‐0.7), high correlation (0.7‐0.9), or very high correlation (0.9‐1.0) [61]. This method will allow us to explore the potential correlation between the constructs of self-management skills and self-regulation skills.

###### Health Care Professionals Level Outcomes – Secondary Outcome Measures

To evaluate the effect of the training on self-management support skills, we will use the data from the SEPSS-36 in a 2-level regression model with measurement occasions within a health care professional.

For the video observations, the video recordings will be broken down into 5-minute intervals. Each interval will be coded independently by 2 researchers according to the NCIT and COUNCEL-CCE coding manuals. Results will be presented with descriptive statistics. Differences in observations through time will be tested with (multilevel) regression analyses for repeated measures.

###### Setting Level Outcomes – Cost-Effectiveness

Burn care costs will be calculated by multiplying the volumes of health care used by the corresponding unit prices. The unit prices were derived from the Dutch guidelines [62] and previous studies [63-65]. The unit prices of previous studies will be updated by the inflation correction of the current financial year. Substantive additions, for instance, patients’ costs will be based on previous studies and current care.

Utility values will be obtained from each patient with and without the BreeZe intervention by using the EQ-5D-5L questionnaire. The utility scores per domain range between 0 and 1, whereas 0 is death and 1 is perfect health. The total utility score per patient will be calculated. Quality-adjusted life years will be calculated by multiplying the length of time spent in a particular health state by its associated utility score.

### RE-AIM: Adoption

At the staff level, adoption will be assessed with the results of the PRESS at 6 months post implementation, presented using descriptive statistics. At the setting level, adoption will be assessed by conducting CFIR-informed interviews with all participating health care professionals. These interviews will be transcribed verbatim and analyzed using a thematic content analysis using ATLAS.ti. Furthermore, 2 researchers will independently code each interview. Then, the researchers organize codes into categories and identify key themes that reflect adoption-related data.

### RE-AIM: Implementation

To assess intervention fidelity, health care professionals are asked to document in patient records if, when, and which components of the BreeZe intervention they have used (eg, the Self-management web, goal setting, and action planning). This documentation will be used to assess how often certain components are used.

To assess implementation fidelity to the implementation strategies, the results of the implementation plan will be analyzed and presented with descriptive statistics (eg, completing the e-learning, attending the training, and being exposed to the additional ERIC implementation strategies).

Furthermore, to gain insight into the adaptations made to BreeZe or to the burn center (eg, workflows), we analyze the adaptations that have been documented during the study. These results will be schematically presented and summarized in text.

### RE-AIM: Maintenance

At the individual health care professional level, maintenance will be assessed by using the results of the SEPSS-36 at 12 months post implementation (refer to Health Care Professional Level Outcomes – Secondary Outcome Measures). Furthermore, the PRESS outcomes at 12 months post implementation will be presented using descriptive statistics.

At the setting level, maintenance will be assessed by using the results of the CSAT questionnaire. Results of each center will be separately presented. First, descriptive statistics will be presented for both the total score as well as the scores of each subdomain. Second, an independent *t* test or a Mann-Whitney test will be used to assess the difference in results over time.

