### RE-AIM: Adoption

Adoption of the intervention will be measured at the staff and setting level. At the staff level, we will assess whether the intervention is adopted by conducting CFIR-informed interviews with burn physicians, nurse practitioners, and aftercare nurses, by asking if they use the BreeZe intervention in their daily work. These interviews will provide working hypotheses to explain the degree of individual intervention adoption. At the setting level, we will assess whether the BreeZe intervention is used within an individual burn center.

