### Participant Timeline

The participant timelines illustrated in Table 2 (for survivors of burn injuries) and Table 3 (for health care professionals) outline the different assessment time points of the study.

**Table 2. T2:** Timeline for participating survivors of burn injuries: enrollment, interventions, and assessments.

	Study period – survivors of burn injuries				
	Enrollment	Allocation	Postallocation		Closeout
	Before discharge	At discharge	T1 (2 weeks postdischarge)	T2 (6 months postdischarge)	T3 (12 months postdischarge)
Enrollment					
Eligibility screen	✓				
Informed consent	✓				
Allocation		✓			
Interventions					
Control (usual care)^a^			✓	✓	✓
BreeZe aftercare^a^			✓	✓	✓
Assessments					
Demographics		✓			
Self-management skills (PiH^b^) [34]			✓	✓	✓
Self-regulation (SeRA^c^) [35]			✓	✓	✓
Participation (MeEAP^d^) [36]			✓	✓	
Daily activities (EQ-5D-5L) [37]			✓	✓	✓
Self-care (EQ-5D-5L) [37]			✓	✓	✓
Dependency			✓	✓	✓
Return to work or school (ICHOM^e^) [38]				✓	✓
Patient centeredness (CAHPS^f^) [39,53]				✓	
Quality of life (EQ-5D-5L) [37]			✓	✓	✓

a Duration of usual or BreeZe aftercare depends on the personal trajectory of the survivor of burn injuries.

b PiH: Partners in Health scale.

c SeRA: Self-Regulation Assessment.

d MeEAP: Measure of Experiential Aspects of Participation.

e ICHOM: Adjusted International Consortium for Health Outcomes Measurement.

f CAHPS: Consumer Assessment of Health Plan Survey.

**Table 3. T3:** Timeline for participating health care professionals: enrollment, interventions, and assessments.

	Study period – health care professionals				
	Enrollment	Allocation	Postallocation		Closeout
	Preimplementation phase	Implementation phase	T1 (3 months postimplementation phase)	T2 (6 months post implementation phase)	T3 (12 months postimplementation phase)
Enrollment					
Eligibility screen	✓				
Informed consent	✓				
Allocation		✓			
Interventions					
Training		✓			
Assessments					
Demographics	✓				
Self-management support skills (SEPSS-36^a^) [40]	✓		✓	✓	✓
Need-supportive counseling (COUNSEL-CCE^b^ and NCIT^c^) [41,42]	✓		✓		✓
Maintenance (PRESS^d^) [44]				✓	✓
Maintenance (CSAT^e^ ) [45]			✓		✓
CFIR^f^-informed interviews				✓	

a SEPSS-36: Self-Efficacy and Performance in Self-Management Support Questionnaire.

b COUNSEL-CCE: Coding and Observing Need-Supportive Counselling in Chronic Care Encounters.

c NCIT: Nurse-Child Interaction Taxonomy.

d PRESS: Provider Report of Sustainment Scale.

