#### Health Care Professionals

Information on eligible health care professionals will be included in a password-protected eligibility file in Excel, which will be stored on a protected working drive. The password of the eligibility file is only known by the involved researchers. For entry in the eligibility file, the characteristics of eligible health care professionals that are documented are name, years of experience within the profession (divided into categories), and participation (yes or no).

Informed consent will be taken on paper and stored in a locked cupboard at the research office of each burn center. After taking informed consent, each health care professional will be assigned a unique study code in a password-protected key data file in Excel.

Questionnaires will be sent out on paper or via Castor [60]. Data from paper questionnaires will be imported into an Excel file and then transported into SPSS or MLwiN (Center for Multilevel Modelling, University of Bristol) [57]. Video recording files will be directly transferred from the video camera to the research working drive. Interview recordings will be directly transferred from the tape recorder to the research working drive, and then transported into Atlas.TI.

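### CSAT change over time is tested with unpaired tests although the staff answers are largely paired; separately, adoption is measured differently in two sections and needs reconciling

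*Protocol article*

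**What the plan says.** **CSAT.** The Maintenance section of Statistical Methods describes CSAT scores first, with the statement "Results of each center will be separately presented". It then says that an independent *t* "test or a Mann-Whitney test will be used to assess the difference in results over time". Both named tests are for independent samples. Table 3, titled "Timeline for participating health care professionals: enrollment, interventions, and assessments", ticks the CSAT at 3 and 12 months post implementation, so the comparison over time is between those two occasions. Under Data Management, "each health care professional will be assigned a unique study code in a password-protected key data file in Excel". For the SEPSS-36, the other staff questionnaire tested over time, the plan is a "2-level regression model with measurement occasions within a health care professional".

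**Adoption.** In the Outcomes section, at staff level, "we will assess whether the intervention is adopted by conducting CFIR-informed interviews with burn physicians, nurse practitioners, and aftercare nurses". At setting level the Outcomes text asks whether BreeZe is used within each center, and Table 1 names project coordinator records as the source. In Statistical Methods, staff-level "adoption will be assessed with the results of the PRESS at 6 months post implementation", and setting-level adoption comes from the CFIR-informed interviews. Table 1 and Table 3 list the PRESS only under maintenance, and the Outcomes text on maintenance uses it there at 6 and 12 months. The Statistical Methods text on maintenance uses only the 12-month PRESS.

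**The concern.** An independent-samples test treats the 3-month and 12-month CSAT answers as coming from different people. If they come mostly from the same people, the test ignores the correlation between a person's two scores and overstates the standard error of the change. The Confidentiality section acknowledges that few professionals take part, and CSAT results are presented by center, so little information is available and discarding the pairing is costly. What is at stake is whether a real gain or loss in a center's capacity to sustain BreeZe is detected.

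The adoption issue is of a different kind. Adoption is one of the coprimary implementation outcomes, and two sections of the article measure it differently at both levels. Until they are reconciled, the choice of measure can be made after the data are seen.

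**Working it through.** **CSAT: inputs.** From the protocol: unpaired tests, occasions at 3 and 12 months, one study code per professional, significance at .05 (taken as two-sided). Not given: the number of professionals per center, the CSAT standard deviation and the within-person correlation r. Assumed here: n = 5, 10 or 20 per center, r from 0 to 0.7, and a fixed shift of 0.8 SD. The protocol states no power figure for this test, so there is none to reproduce.

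**Standard error.** With n people measured twice and common variance σ², the change in means has true variance 2σ²(1 − r)/n. The independent test uses 2σ²/n. Its standard error is therefore too large by the factor 1/√(1 − r): 1/√0.7 = 1.20 at r = 0.3, 1/√0.5 = 1.41 at r = 0.5, and 1/√0.3 = 1.83 at r = 0.7.

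**Type I error.** In large samples the true size is 2[1 − Φ(1.96/√(1 − r))], which gives 0.019, 0.0056 and 0.0003 at r = 0.3, 0.5 and 0.7. These formulas are optimistic for small groups, so the independent and paired *t* tests were also simulated (bivariate normal scores, 40,000 replicates per cell). At n = 10 the independent test's size was 0.022, 0.009 and 0.002. The paired test stayed at 0.048 to 0.051 in every scenario.

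**Power for a fixed 0.8 SD shift (simulated).**

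| n | r | Independent *t* | Paired *t* |
|---|---|---|---|
| 5 | 0.5 | 0.16 | 0.29 |
| 5 | 0.7 | 0.13 | 0.42 |
| 10 | 0 | 0.39 | 0.36 |
| 10 | 0.3 | 0.38 | 0.48 |
| 10 | 0.5 | 0.36 | 0.62 |
| 10 | 0.7 | 0.35 | 0.83 |
| 20 | 0.5 | 0.76 | 0.93 |
| 20 | 0.7 | 0.81 | 0.99 |

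At n = 10 the power of the independent test hardly moves with r. The loss is the gain from pairing that is forgone. At r = 0 the two tests are about equal, with the independent test marginally ahead. The Mann-Whitney test was not simulated, but it rests on the same independence assumption.

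**Adoption: the passages side by side.**

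| | Outcomes text and Table 1 | Statistical Methods |
|---|---|---|
| Adoption, staff level | CFIR-informed interviews | PRESS at 6 months |
| Adoption, setting level | Use within the center; coordinator records | CFIR-informed interviews |
| PRESS at 6 months | Maintenance | Adoption |
| PRESS at 12 months | Maintenance | Maintenance |

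Both adoption rows differ, and so does the role of the 6-month PRESS. No arithmetic applies.

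**The case against.** **Pairing is inferred.** No sentence says that the same individuals answer the CSAT both times. Table 3 and the study codes make it likely, but staff turnover over nine months would leave the data only partly paired. This stands as a qualification. It bears on the choice of remedy, because a purely paired test would drop unmatched respondents, but an unpaired test would still ignore the pairs that exist.

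**The direction is conservative.** A reader might infer that the test could produce false claims of change, or that the maintenance result as a whole is unsound. Neither follows. With positive correlation the test rejects too rarely, and maintenance also rests on the descriptive CSAT results, PRESS, SEPSS-36 and interviews, none of which depends on this test.

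**The size can be overstated.** If the effect is set at whatever a paired test detects with 80% power, the large-sample power of the unpaired test is 1 − Φ(1.96/√(1 − r) − 2.80), or 51%, 22% and 6% at r = 0.5, 0.7 and 0.8. That invites the inference that its power collapses as r rises. But the effect so defined shrinks with √(1 − r): at r = 0.8 it is √(0.2/0.5) = 63% of its value at r = 0.5. For a fixed shift there is no such collapse, as the simulation shows.

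**Adoption.** Within Statistical Methods the PRESS is split cleanly by time, and the overlap arises only against the Outcomes text and tables. The article also refers detailed RE-AIM definitions to Multimedia Appendix 1, which is not shown. A reader might infer that adoption has no single definition anywhere; the documents at hand cannot establish that. The inconsistency within the article remains.

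**Conclusion.** The CSAT over-time test is wrong as written. Under assumed values of n = 10 and r = 0.5 its true type I error is about 0.9% instead of 5%, and its power for a 0.8 SD shift is about 0.36 where a paired test has 0.62; at r = 0.7 the figures are 0.35 and 0.83. If r is near zero the choice matters little. The result rests on mostly the same professionals answering twice, on positive within-person correlation, and on assumed staff numbers, correlations and shift. The consequence is that a real change in sustainability may be missed, and it is confined to this one test.

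For adoption, the sections contradict each other at both levels. Nothing is miscalculated, but a coprimary outcome should not enter analysis with its measure open. Neither issue touches the comparison of self-management skills.

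**What to change.** **CSAT.** Replace the independent *t* and Mann-Whitney tests with the same 2-level model as the SEPSS-36, with occasions nested within professional. This also keeps professionals who answer only once. If nearly all respondents are matched, a paired *t* test or Wilcoxon signed-rank test would do. The separate descriptive results by center can stay as planned.

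**Adoption.** State one measure for staff level and one for setting level, and use them consistently in Table 1, in the Outcomes text on adoption and maintenance, and in the Statistical Methods text on both. Assign the 6-month PRESS to one dimension. Choose from measures the protocol already names. A new ratio built from documented BreeZe components should be avoided: patient records are the source for intervention fidelity, and the Outcomes section samples them only by convenience, so the count might not be available for every professional.

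**Cost.** Both changes are to wording, with no new participants or questionnaires; the study codes should allow the CSAT answers to be linked. They should be made before data analysis starts, which the Results section gives as August 2026.

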#### Health Care Professionals

Depending on the burn center and the complexity of the patient, a burn physician, nurse practitioner, or aftercare nurse is assigned the role of care coordinator in burn aftercare, putting them in the position to systematically provide self-management support. Therefore, all nurse practitioners, aftercare nurses, and burn physicians will be invited to participate and receive training.

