### Statistical Methods

#### Statistical Methods for Primary and Secondary Outcomes

##### Overview

All quantitative analyses will be conducted using MLwiN 3.10 for nested data or IBM SPSS Statistics [57]. A *P* value <.05 will be considered statistically significant. For all outcomes, descriptive statistics will be used to present demographics and outcomes, using frequencies (%) for categorical variables, and median and IQR (if nonnormally distributed) or mean and SD (if normally distributed) for continuous variables.

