#### Health Care Professionals

Due to the small number of health care professionals in our study, we will adjust the data collection of the demographics. To maintain confidentiality, age and years of experience will be collected in categories, with 5-year steps. In addition, all health care professionals will be assigned a unique study code (key). For further data collection, only the study code will be assigned to the data. Only the main researchers have access to the key document with participants’ names. No identifying information will be published.

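### The independent-samples difference test planned for CSAT scores cannot show that setting-level maintenance held, and with few staff a nonsignificant result says almost nothing

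*Protocol article*

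**What the plan says.** The Objectives section of the protocol article places maintenance among the implementation outcomes of the second coprimary objective. At setting level it is measured with the CSAT (35 items, 7 domains, score range 0 to 245 in Table 1). Table 3 schedules the CSAT for participating health care professionals at 3 and 12 months post implementation.

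The analysis is in RE-AIM: Maintenance under Statistical Methods. For inference it names two alternatives, a t test for independent samples and the Mann-Whitney procedure, and says that the chosen "test will be used to assess the difference in results over time". Reporting is by center: "Results of each center will be separately presented". Summaries of total and subdomain CSAT scores come before any testing. The general threshold, in the Overview of Statistical Methods, is that a *P* "value <.05 will be considered statistically significant".

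No section states how many professionals will answer. The Confidentiality section refers to them with the words "Due to the small number of health care professionals in our study". The eligibility section limits training to three professions: "all nurse practitioners, aftercare nurses, and burn physicians will be invited to participate and receive training".

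CFIR-informed interviews are a further source for setting-level maintenance. In the Outcomes text their role is to generate hypotheses that explain how far maintenance was achieved.

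**The concern.** Maintenance at setting level asks whether a center's capacity to sustain BreeZe held up between 3 and 12 months. A difference test answers a different question, namely whether there is evidence of change. If capacity held, the expected result is nonsignificant, but a small sample produces that same result whether or not capacity held. The test therefore does not separate a center that sustained its capacity from one that lost a meaningful amount of it.

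The specified tests are also for independent samples, while Table 3 follows the same participating professionals over time. For the SEPSS-36 in these professionals, the article plans a two-level model with occasions nested within the professional. The CSAT plan does not use that structure, which costs further power where numbers are already low.

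At stake is the interpretation of one component of a coprimary outcome. A report of no significant change in each center could be taken as reassurance that the data do not give.

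**Working it through.** The plan gives no sample size, SD, effect size or power for the CSAT, so there is no stated figure to reproduce.

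**Inputs from the article**
- Test: independent t or Mann-Whitney, two occasions (3 and 12 months), results shown by center.
- Significance level: 0.05.

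**Assumptions**
- Two-sided testing. The article states this only for the sample size of the patient outcome.
- n responders per center per occasion: 4 to 15, extended upward to see where the conclusion changes.
- True decline of 0.5 SD, as a benchmark.
- Within-person correlation r between occasions: 0.5 or 0.7.

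**Step 1. Independent t test as planned, treating the two occasions as unrelated.** Power comes from the noncentral t distribution with 2n − 2 degrees of freedom and noncentrality 0.5 × √(n/2). For n = 10 the noncentrality is 0.5 × √5 = 1.118, the critical value is 2.101 and power is 18.5%, so the miss rate is 81%.

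| n per occasion | Miss rate, 0.5-SD decline |
|---|---|
| 4 | 91% |
| 6 | 88% |
| 8 | 85% |
| 10 | 81% |
| 15 | 74% |
| 20 | 66% |
| 30 | 52% |

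The miss rate stays above 50% up to n = 31 and falls just below it at n = 32. Power of 80% needs n = 64 per occasion.

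**Step 2. Same staff measured twice, pairing ignored.** Simulation with r = 0.5 gives the independent t test power of about 6% (n = 5), 12% (n = 10) and 20% (n = 15), so miss rates of about 94%, 88% and 80%. Its actual type I error falls to roughly 1%, because the standard error is too large for positively correlated data. Mann-Whitney power is about 4%, 11% and 17%.

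**Step 3. Pairing respected.** The noncentrality is √n × 0.5/√(2(1 − r)), with n − 1 degrees of freedom.

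| n | Miss rate, r = 0.5 | Miss rate, r = 0.7 |
|---|---|---|
| 4 | 89% | 85% |
| 6 | 83% | 75% |
| 8 | 77% | 65% |
| 10 | 71% | 55% |
| 15 | 56% | 36% |

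Pairing helps clearly, but a nonsignificant paired test within one center would still be weak evidence of no decline.

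**Step 4. What an interval shows.** The 95% CI half-width for the independent comparison is t × √(2/n) in SD units. At n = 10 it is 2.101 × √0.2 = 0.94 SD, and at n = 15 it is 0.75 SD. A center with no observed change could not exclude a half-SD loss. For the within-person change the half-width is t × √(2(1 − r)/n). At n = 10 and r = 0.5 it is 2.262 × √0.1 = 0.72 SD. Pooling an assumed 30 staff, with center as a fixed effect (27 degrees of freedom), it is 2.052 × √(1/30) = 0.37 SD, which could exclude a half-SD loss when the observed change is near zero.

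**The case against.** The strongest reply is that the article contains no decision rule. A reader might infer that each center without a significant change will be declared maintained, which would make the conclusion nearly automatic. The documents do not support that reading: the text says only that the difference over time will be assessed. This part of the objection stands.

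It is also fair that setting-level maintenance does not depend on the test alone. Descriptive CSAT scores come first and interviews contribute. Maintenance as a whole has a staff level too, with the PRESS and the SEPSS-36. The interviews, however, are there to explain the degree of maintenance, and descriptive scores alone do not quantify uncertainty about change.

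Staff numbers, the half-SD benchmark and the correlations are assumptions. It is also not fully explicit that the test is run within each center, although separate presentation makes that the natural reading. If it were pooled, the independent test would miss 52% with 30 staff in all, but only 22% with 60. The strong statement therefore belongs to the per-center analysis.

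Finally, a margin for relevant decline is the kind of detail commonly left to an SAP, and the documents offer no basis for setting one. Its absence is not the point made here. The point is that the method the article does state does not answer the maintenance question and ignores the repeated measurement of the same staff.

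**Conclusion.** The concern holds in limited form. For setting-level maintenance, the only inferential step stated is a difference test for independent samples. With 4 to 15 responders per center, the planned t test misses a half-SD decline in 91% to 74% of cases. The rate is higher if the same people answer twice with positively correlated scores. The per-center finding does not depend closely on the unstated staff number, since the miss rate exceeds 50% for any center with 31 or fewer responders per occasion. A nonsignificant result is therefore close to uninformative about whether capacity held, and could be misread as maintenance. The article does not say that it will be. The point affects one component of a coprimary outcome and is cheap to repair.

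**What to change.** In RE-AIM: Maintenance under Statistical Methods, replace the independent t or Mann-Whitney test as the basis for inference. Report the mean within-person CSAT change from 3 to 12 months with its 95% CI, per center and pooled over the three centers with center as a fixed effect. Use the repeated-measures approach already planned for the SEPSS-36. Keep the descriptive statistics. State that a nonsignificant change will not be taken as evidence of maintenance, and that a result is inconclusive where the interval still includes a decline the team considers relevant. The team should record that judgment before analysis starts, which the Results section puts at August 2026.

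The cost is a change of wording and no new data. Within-person change requires that the two CSAT questionnaires can be linked, which the unique study codes for professionals should allow. The downside is that per-center results will often be inconclusive, which is what so few respondents can support.
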